#### Mental health service linkage

This measure will be based on caregiver or patient report of linkage to any mental health service either internal Rady or external/outside of Rady following elevated depression score. Values will be collected at 3 months and 6 months.

### Setting factors

#### Medical clinic characteristics

Medical clinic characteristics recorded for the study will include number of clinicians, average patient volume, patient-case mix (child race/ethnicity), preferred language, health insurance (public vs private), gender/sex, and age. These will be derived from the EHR and team members and recorded at baseline.

### Data management

#### Analytic plan

For Aims 2 and 3, we will use multilevel modeling with random intercepts and slopes to test the preliminary effects of TCT on implementation and service outcomes (Aim 2) and mechanisms (Aim 3). Refer to Table 2 for measures of outcomes and mechanisms. Specifically, outcomes include team member-reported acceptability, appropriateness, feasibility and workflow efficiency, and child service outcomes. Potential mechanisms are the proposed mediators of implementation climate, psychological safety climate, communication/coordination, and shared cognitions (see Table 2). Clinic will be included as a covariate (fixed effect). To test the effects of TCT a Group [current implementation vs. TCT] X Time [Baseline, 3, 6 Months] cross-level interaction will be assessed for each outcome. If a statistically significant (*p* < .05) interaction term is evident, simple slopes analyses will be conducted.

Quantitative data and qualitative data will be first analyzed separately. First, quantitative analyses of mechanisms of the TCT implementation strategy will be analyzed using the analytic approach described in Aim 2. To examine the hypothesized mediated effects of implementation strategy condition on implementation and service outcomes, multilevel path analysis will be conducted. Measures of Implementation Climate, Intra-Organizational Alignment, Communication and Coordination, Shared Cognitions, and Psych Safety will be tested as mediators in respective models. The specific mediated effects within these models will be tested using the bias-corrected bootstrap approach [38]. Qualitative interview data will be analyzed using rapid qualitative methods [28] based on a templated summary, deductive approach focused on specified team mechanisms. Specifically, the research team will code transcripts for changes in proposed mechanisms as explanatory factors in implementation and service outcomes. We will then use a mixed-methods analytic approach to synthesize the qualitative and quantitative data collected to examine convergence (i.e., do the two methods confirm or find similar results), complementarity (i.e., do the two methods provide more depth of understanding of research questions), and expansion (i.e., do the two methods provide insights beyond either method alone).

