Aim 2 will utilize a cluster randomized design in which four specialty care clinics (10 clinicians per clinic; *n* = 40 clinicians) responsible for reviewing and responding to depression screening (youth ages 12–17 years) will be matched and then randomized to a TCT condition (two clinics) versus an early identification universal depression screening condition (two clinics). Clinics will be matched on team size, makeup of the team members, type of medical care focus and then randomized to conditions. Thus, there will be two sets of two matched clinics that will then be randomized, one to the TCT and the other to early identification universal depression screening condition. In the comparison implementation strategy (early identification universal depression screening), multiple discrete strategies will be used including depression screening training in which providers and staff are provided 1) training in the depression screening tool (PHQ), 2) orientation to the clinical pathway (i.e., screening conducted at every urgent care or emergency department visit and every 30 days for all other medical visits), and 3) expectations for handoff to the next step in the care cascade.

The TCT will last 6 months and is proposed to include the following components that will be refined based on Aim 1 findings and developmental activities: Two initial 2-h didactic sessions on effective communication between team members (information-based methods) and simulation exercises based on mock clinical cases (practice-based methods), biweekly performance feedback about intra-team communication in the EHR (demonstration-based methods) provided during regularly scheduled supervision meetings, and a 1 h booster coaching sessions approximately every 2 months over a 6-month period.

#### Specific Aim 3

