#### Workflow efficiency

Workflow efficiency is a primary outcome for the Aim 2 trial that will be assessed through two different measures. The first, referral processing, will be obtained by capturing the time from screening to referral via EHR (Epic) timestamps. The second, referral quality, will be based on provider reports of referral to appropriate service following depressions screening. Both measures will be collected at the 6-month timepoint following completion of the Aim 2 trial.

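### Clinic as a fixed effect leaves no estimable TCT effect for outcomes measured only at 6 months, and the plan states no clinic-by-time variation for the Group x Time test of repeated outcomes

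*Protocol article*

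**What the plan says.** Specific Aim 2 enrols "four specialty care clinics (10 clinicians per clinic", 40 clinicians in all) and randomises at clinic level: "Thus, there will be two sets of two matched clinics that will then be randomized". One clinic of each pair receives TCT, so there are two clinics per arm.

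The Analytic plan states "we will use multilevel modeling with random intercepts and slopes to test the preliminary effects of TCT" without naming the level of those random effects, and adds "Clinic will be included as a covariate (fixed effect"). The effect of TCT is to be judged by a Group x Time term over baseline, 3 and 6 months. This "cross-level interaction will be assessed for each outcome", and if a significant (p < .05) "interaction term is evident, simple slopes analyses will be conducted".

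The Workflow efficiency section says "Workflow efficiency is a primary outcome for the Aim 2 trial" and collects both of its measures at 6 months. The section on acceptability, appropriateness and feasibility also gives 6 months as the only time of measurement. EHR clinical outcomes and the climate, safety and collaboration scales are collected at baseline, 3 and 6 months.

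The Power analysis claims 80% power with 20 clinicians per arm. Its inputs include a within-clinician autocorrelation of .70 but no variance component for clinic.

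**The concern.** In a trial that randomises clinics, a clinic's arm is one of its fixed attributes. A model with a free parameter for each clinic has nothing left from which to estimate a constant difference between arms. Repeated measurement partly rescues this, because exposure to TCT starts after baseline and change over time can be compared. But that comparison must then be judged against how much clinics differ from one another in their change, and the plan names no such term.

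Two things are at stake. A stated primary outcome may have no usable analysis. For the repeated outcomes, an event in one clinic over six months, such as staff turnover or a workflow change, could be read as an effect of TCT with more confidence than four clinics can support.

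**Working it through.** **Plan's own figure.** The inputs are d = .61, SDs 1.0/1.5/2.0, AR(1) = .70, 15% attrition (20 per arm becomes 17) and alpha .05, taken as two-sided.
- Linear rise to .61 SD at 6 months: the variance of the baseline-to-6-month difference is 1 + 4 − 2(.49)(1)(2) = 3.04. The SE is √(2 × 3.04/17) = .598, z = 1.22/.598 = 2.04, and power is Φ(2.04 − 1.96) = 53%.
- Single-time comparison: z = .61/√(2/17) = 1.78, power 43%.
- About 80% appears if the variances (not the SDs) rise by .5 and the difference grows 0, .61, 1.22: variance 1 + 2 − 2(.49)(√2) = 1.61, SE .436, z = 2.80, power 80%.

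The plan states neither the trajectory of d nor the sidedness, so 80% is neither confirmed nor refuted. Nothing below depends on it.

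**Outcomes with one wave.** Call the pairs (A, B) and (C, D), with A and C in TCT and A as reference. Then Group = 1 − I(B) − I(D) for every clinician. The columns are the intercept, Group and three clinic dummies: 5 columns, rank 4. If software drops the dummy for D, the model mean is β0 in D and β0 + βGroup in A. The coefficient printed as Group is then the mean of A minus the mean of D, two clinics from different pairs. With one wave there is also no Time term for Group to interact with, however clinic is coded.

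**Outcomes with three waves.** Intercept, Group, three dummies, Time and Group x Time give 7 columns, rank 6, so the Group main effect is again aliased. Without it, 6 columns have rank 6; without Group x Time as well, the rank is 5. Group x Time is therefore estimable. The pair indicator lies in the span of the clinic dummies (rank 4 with or without it), so clinic and pair differences in level are absorbed.

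**Error term for Group x Time.** Write a clinician's change as an arm effect plus a clinic deviation (share ρ of the variance σ²) plus a clinician deviation. With 2 clinics of 10 per arm, the variance of an arm mean is σ²[ρ/2 + (1 − ρ)/20] = (σ²/20)(1 + 9ρ). A test with clinician-level error uses about σ²/20. Approximate type I error is 2[1 − Φ(1.96/√(1 + 9ρ))]. The documents give no ρ; the values are assumptions.

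| Assumed ρ | 1 + 9ρ | Formula | Simulated (40,000 runs, change scores) |
|---|---|---|---|
| 0 | 1.00 | 5.0% | 5.2% |
| .01 | 1.09 | 6.05% | 6.1% |
| .05 | 1.45 | 10.4% | 10.5% |
| .10 | 1.90 | 15.5% | 16.7% |

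In the same simulation, a t-test on clinic mean change (2 df) held 5.0% to 5.1% throughout.

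**Power with the clinic as unit.** Assume the .61 is a difference in change in units of its SD. The SE is √(ρ + (1 − ρ)/10) and the critical t is 4.30 on 2 df or 12.7 on 1 df (paired).
- ρ = 0: SE .316, noncentrality 1.93, power 21% (paired 12%).
- ρ = .05: SE .381, noncentrality 1.60, power 16% (paired 10%).
- ρ = .10: SE .436, noncentrality 1.40, power 14% (paired 9%).

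**The case against.** The strongest reply is that the plan tests Group x Time, not a Group main effect, and that this term is identified. That is right for every three-wave outcome. A reader might infer that the main comparison is unidentified throughout, that the matching is ignored, or that clinic dummies serve no purpose here. The documents do not support any of these: the dummies absorb clinic and pair levels, exposure changes within TCT clinics after baseline, and only pair and clinic differences in change are left out.

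Second, the single-wave problem has two causes. A three-wave interaction is promised for outcomes collected once, and removing the clinic term does not by itself supply the missing test. This stands, and the fix must deal with both. It is also fair to ask whether scales that rate the TCT strategy suit a between-arm comparison at all.

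Third, the level of the random intercepts and slopes is not named, and a random clinic slope would put the missing variation back. That is possible, but with clinic declared fixed the clinician level is the natural reading. A random clinic slope would also leave the single-wave aliasing untouched.

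Fourth, this is a pilot of preliminary effects, and p < .05 formally only triggers simple slopes. This softens the consequence. It does not remove the error, because that threshold is attached to the only stated quantitative test of the TCT effect.

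Finally, the inflation may be larger for youth-level EHR outcomes with many patients per clinic. The protocol gives no count of elevated screens per clinic, so no size is claimed.

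**Conclusion.** The model is wrong as written, in two parts of different strength.

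For outcomes collected only at 6 months, including the primary workflow-efficiency measures, the stated model gives no TCT estimate. This is algebra and needs no assumption beyond whole-clinic randomisation and a fixed clinic effect.

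For three-wave outcomes the estimate exists, but the stated error term lacks clinic-by-time variation. Type I error is about 6%, 10% and 16% at slope ICCs of .01, .05 and .10. This rests on clinician-level random effects, 10 clinicians per clinic and assumed ICCs. A reader might infer that the p < .05 rule is invalid outright; it is invalid only to the extent that the clinic variance in change exceeds zero, a quantity the protocol does not give.

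The wide intervals on 1 or 2 df are a limit of having four clinics, not a product of the fixed effect. The fixed-effect wording hides that limit.

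**What to change.** - **Single-wave outcomes:** drop the clinic fixed effect and the Group x Time test. Summarise each clinic at 6 months and compare the summaries within the two matched pairs. Change from baseline cannot be used here, since no baseline is collected.
- **Repeated outcomes:** compare clinic-level change from baseline within pairs, or keep a mixed model that includes clinic-by-time random variation with small-sample degrees of freedom. The clinic-level comparison is the safer choice, because four clinics barely support a variance estimate. State the level of every random effect.
- **Reporting:** give estimates with confidence intervals on cluster degrees of freedom, labelled preliminary, and make no claim from p < .05.
- **Power analysis:** restate or withdraw the 80%. With the clinic as unit on 2 df, power is about 14% to 21% for a .61 SD difference in change at ICC 0 to .10.

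No change to recruitment or data collection is needed. The cost is much wider intervals and a power section that no longer promises a significance test, which still fits the stated aim of preparing a later definitive trial.

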### Participants

Participants from Aim 1 will be recruited from the outpatient ambulatory departments with the highest rates of depression screening and/or behavioral health referrals based on the most recent patient reports from the EHR. These participants will include clinic leaders who oversee clinical operations including depression screening, clinicians and bedside staff who initiate depression screening such as physicians, nurses, and medical assistants, as well as clinicians who manage triage and referral to behavioral health services including social workers, psychologists, and administrative staff (e.g., patient access representatives).

Participants for Aims 2 and 3 will include 40 clinicians or clinical staff (including physicians, nurses, medical assistants, and mental health providers) drawn from the 4 enrolled specialty care clinics (an average of 10 clinicians per clinic). The specialty care clinic structure comprises all relevant members of the care cascade including a clinician who initiates the depression screening, medical provider who support screening completion, a behavioral health provider who responds to both an elevated depression screen and triages to the patient access representatives who are expected to confirm linkage to a behavioral health provider. Based on data from FY 2023, both inpatient and outpatient specialty services have high rates of depression screening.

Although youth are not participants in this project, the focal pediatric population will be youth ages 12–17 years who have a service encounter in the past year. This age range was selected because it aligns with the age range of the current depression screening protocol at Rady Children’s Health Network [7]. De-identified youth patient data will be abstracted from the EHR to determine movement through the screening-to-treatment cascade and workflow efficiency (i.e., time to complete each step in the cascade and referral quality).

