#### Intra-organizational alignment

Alignment [12, 15] will be measured based on the degree to which team members from different organizational levels (e.g., physicians, nurses, medical assistants, social workers) exhibit similarity on Edmonson’s Psychological Safety climate [36] and the Jacob’s et al. Implementation Climate Measure [33].

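### Mediated effects are to be tested by bias-corrected bootstrap, but condition varies over only four clinics and alignment has one value per clinic, so the tests lack a sound error rate

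*Protocol article*

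**What the plan says.** The Analytic plan fixes both the model and the test. The model: "To examine the hypothesized mediated effects of implementation strategy condition on implementation and service outcomes, multilevel path analysis will be conducted". The mediators: "Measures of Implementation Climate, Intra-Organizational Alignment, Communication and Coordination, Shared Cognitions, and Psych Safety will be tested as mediators in respective models". The test: "The specific mediated effects within these models will be tested using the bias-corrected bootstrap approach". It names no resampling unit, and it enters clinic as a fixed-effect covariate.

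The design is in Study objectives, under Specific Aim 2. Four specialty clinics are "matched and then randomized to a TCT condition (two clinics) versus an early identification universal depression screening condition (two clinics"), with the matching described as "Thus, there will be two sets of two matched clinics that will then be randomized". The Participants section gives 40 clinicians or clinical staff "drawn from the 4 enrolled specialty care clinics (an average of 10 clinicians per clinic").

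Alignment "will be measured based on the degree to which team members from different organizational levels" resemble each other on the psychological safety and implementation climate measures. Table 2 lists it as a team-level mechanism. On patients, the Participants section says that youth are not study participants and that "De-identified youth patient data will be abstracted from the EHR". No link from a youth to an individual clinician is described.

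**The concern.** A bootstrap interval for an indirect effect is only as good as the independent units behind it. Here the exposure is constant within clinic and there are four clinics. One of the five mediators, alignment, is by its definition a property of the team, so it too has four independent values. If clinicians are resampled as though they were independent, clinic-to-clinic variation is left out of the interval. If clinics are resampled, there are too few of them for a bootstrap distribution to mean much.

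Aim 3 is where the trial learns about mechanisms. The Discussion says that these data will be essential preliminary evidence for a later definitive test and will be used to refine the training model. A mediation test that rejects too often could carry a mechanism forward that the data do not support.

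**Working it through.** **Plan's own figure.** There is none for mediation. The 80% in the Power analysis section concerns the group comparison, so nothing needs to be reproduced here.

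**Inputs from the article.** 4 clinics, 2 per arm, 2 matched pairs (Specific Aim 2); about 10 clinicians per clinic, 40 in all (Participants); alignment measured by team (Table 2 and its own section); autocorrelation .70 (Power analysis).

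**Assumed, because the article gives no value.** Clinic ICC; the mediator-to-outcome coefficient b; the number of youths per clinic. The nominal level is taken as two-sided 5%.

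**Degrees of freedom between clinics**
- Condition to mediator: 4 clinics - intercept - condition = 2 (critical t 4.30). Keeping the matched pair leaves 4 - 3 = 1 (critical t 12.7).
- Clinic-level outcome on condition and alignment: 4 - intercept - condition - alignment = 1 (critical t 12.7). Adding the pair would leave 0.
- Three time points give 4 x 3 = 12 alignment values, still from four independent clinics.

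**Randomisation limit for condition.** The smallest two-sided p is 2/4 = .50 with matched pairs, or 2/6 = .33 if pairing is ignored.

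**Resampling clinics**
- Two draws from two clinics give 3 distinct samples per arm, so 3 x 3 = 9 in all.
- A single clinic is drawn twice in both arms with probability 1/2 x 1/2 = 25%. Alignment and condition are then collinear and the alignment slope cannot be estimated.
- Ignoring arm, there are 35 distinct samples, and 2 x (1/2)^4 = 12.5% of draws lose a whole arm.

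**False-positive rate, clinician-reported mediator and outcome**

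Mediator M = u(clinic) + e; outcome Y = bM + v(clinic) + f. The clinic terms have variance ICC and the individual terms 1 - ICC. The effect of condition on M is a = 0, so the true indirect effect is zero. The model is cross-sectional with 4 x 10 clinicians, 1,200 to 1,500 data sets per scenario and 800 to 1,000 bootstrap draws. Repeat runs differ by about two points.

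| Clinic ICC | Clinicians resampled, bias-corrected, b = .39 to .59 |
|---|---|
| .05 | about 13-15% |
| .10 | about 18-21% |
| .20 | about 27-31% |

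- At ICC 0, or with change scores (autocorrelation .70) and a purely persistent clinic effect at ICC .10: about 6-10%.
- Parametric bootstrap from a random-intercept model, b = .6: 13%, 17% and 23% at ICC .05, .10 and .20 (7% at ICC 0).
- Clinics resampled within arm: 37-38% at b = .6 and 31-33% at b = .3, for ICC 0 to .20.
- Percentile instead of bias-corrected interval, clinicians resampled, ICC .10: about 10-18%.

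**False-positive rate, alignment mediator and youth outcome**

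This assumes that youths connect to alignment only through the clinic. Both paths are null and youths are resampled within clinic.

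| Youths per clinic | ICC .01 | ICC .05 | ICC .10 |
|---|---|---|---|
| 25 | 8% | 21% | 32% |
| 100 | 17% | 44% | 57% |

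At ICC 0 the rate is 5-6%.

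**The case against.** The strongest reply is that the planned models are longitudinal and include clinic as a fixed effect, so stable clinic differences drop out. This has force: when the clinic effect is purely persistent and change scores are analysed, the error rate falls to about 6-10%. It does not cover everything. Acceptability, appropriateness and feasibility are collected only at 6 months and cannot be differenced. For them, condition plus clinic fixed effects has 5 columns but rank 4, so the condition effect cannot be separated from clinic. Clinic-by-time variation would also survive differencing.

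A second reply is that four of the five mediators are measured on individuals, so for clinician-reported outcomes the mediator-to-outcome path rests on 40 people. That is right, and the 1-degree-of-freedom argument does not extend to that path. The condition path stays limited to four clinics.

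Third, the link of youth outcomes to mediators through the clinic is inferred. De-identification removes patient identifiers; it need not remove the treating clinician. The point on youth outcomes is therefore conditional.

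Fourth, the resampling unit and the wave of each mediator may be fixed in an analysis plan that is not shown. Their absence is no fault in itself. The difficulty is that neither clinicians nor clinics as the unit gives a sound test once clinics vary.

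Finally, this is a pilot with effects called preliminary, and the mediation results are combined with qualitative data. That lowers the stakes but does not correct the error rate.

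**Conclusion.** The concern holds in a limited form. Four clinics cannot support a formal test of mediation through alignment for a clinic-level outcome: 1 residual degree of freedom and 9 distinct clinic resamples. The same holds for youth outcomes if they meet the mediators only at clinic level. For other clinician-level indirect effects, a bias-corrected bootstrap over clinicians rejects well above 5% in a cross-sectional model once clinics differ: about 18-21% at an assumed ICC of .10.

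Three stronger readings are tempting, and the article does not support them:
- That every planned mediation test is invalid by a known amount. The simulated rates rest on an assumed ICC and b and a cross-sectional model. They are near nominal at ICC 0 and about 6-10% for change scores with persistent clinic effects.
- That mediators and outcomes are both taken at 6 months. Climate, psychological safety and collaboration are also measured at baseline and 3 months, and the Analytic plan does not say which wave enters the path model.
- That mediation p-values will decide which mechanisms enter the definitive trial. The Discussion speaks only of preliminary data and refinement.

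**What to change.** In the Analytic plan, replace testing of mediated effects with exploratory estimation and state that no significance claims will be made. Then:

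- Report alignment descriptively, as four clinic values per time point. Do not test mediation through alignment, or mediation of youth outcomes that runs through the clinic.
- Report target engagement, meaning the difference between arms in change, for each mechanism with repeated measures. Show it by clinic and matched pair, and state that between-clinic inference has only 1 to 2 degrees of freedom, so any interval will be very wide.
- Where an indirect effect is shown, pair the 3-month mediator with the 6-month outcome where both exist.
- Do not offer percentile intervals as a remedy for clustering; they still over-reject when clinics differ.
- Reconcile Table 2, which appears to place shared cognitions at baseline, 3 and 6 months, with the card-sorting section, which places the task after the training is completed. If the latter governs, there is no 3-month value and no change score for that mechanism.

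This is a change of wording; data collection and the qualitative mechanism work are untouched. The cost is the loss of formal mediation p-values, which four clinics cannot support.
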